## Abstract

**Background:**

Infections are the leading cause of death in the acute phase following spinal cord injury and qualify as independent risk factor for poor neurological outcome (“disease modifying factor”). The enhanced susceptibility for infections is not stringently explained by the increased risk of aspiration in tetraplegic patients, neurogenic bladder dysfunction, or by high-dose methylprednisolone treatment. Experimental and clinical pilot data suggest that spinal cord injury disrupts the balanced interplay between the central nervous system and the immune system. The primary hypothesis is that the **S**pinal **C**ord **I**njury-induced **I**mmune **D**epression **S**yndrome (SCI-IDS) is 'neurogenic’ including deactivation of adaptive and innate immunity with decreased HLA-DR expression on monocytes as a key surrogate parameter. Secondary hypotheses are that the Immune Depression Syndrome is i) injury level- and ii) severity-dependent, iii) triggers transient lymphopenia, and iv) causes qualitative functional leukocyte deficits, which may endure the post-acute phase after spinal cord injury.

**Methods/Design:**

SCIentinel is a prospective, international, multicenter study aiming to recruit about 118 patients with acute spinal cord injury or control patients with acute vertebral fracture without neurological deficits scheduled for spinal surgery. The assessment points are: i) <31 hours, ii) 31–55 hours, iii) 7 days, iv) 14 days, and v) 10 weeks post-trauma. Assessment includes infections, concomitant injury, medication and neurological classification using **A**merican Spinal Injury Association **i**mpairment **s**cale (AIS) and neurological level. Laboratory analyses comprise haematological profiling, immunophenotyping, including HLA-DR expression on monocytes, cytokines and gene expression of immune modulators. We provide an administrative interim analysis of the recruitment schedule of the trial.

**Discussion:**

The objectives are to characterize the dysfunction of the innate and adaptive immune system after spinal cord injury and to explore its proposed 'neurogenic’ origin by analyzing its correlation with lesion height and severity. The trial protocol considers difficulties of enrolment in an acute setting, and loss to follow up. The administrative interim analysis confirmed the feasibility of the protocol. Better understanding of the SCI-IDS is crucial to reduce co-morbidities and thereby to attenuate the impact of disease modifying factors to protect neurological “outcome at risk”. This putatively results in improved spinal cord injury medical care.

**Trial registration:**

DRKS-ID: DRKS00000122 (German Clinical Trials Registry)

## Background

The effective treatment of worldwide 2.5 million paralyzed, spinal cord injured patients represents an unmet medical need to date [1]. In addition, the numbers of non-traumatic cases (e.g. tumor, cervical spondylotic myelopathy) of spinal cord injury (SCI) are increasing. Infections, i.e. pneumonia and urinary tract infections are a leading cause of morbidity and mortality in patients with acute SCI [2,3]. However, attributing infections to motor-paralysis related dysfunction alone does not sufficiently explain the increased susceptibility to develop infections after SCI. Among others, dysphagia occurs also in healthy patients over night without causing pneumonia. Thus, higher rates of dysphagia in SCI patients with cervical lesions do not solely explain increased rates of pneumonia.

It has been elucidated recently that SCI might increase predisposition to infections by Central Nervous System (CNS)-specific mechanisms: CNS-injury induces a disturbance of the normally well-balanced interaction between the immune system and the CNS resulting in a Spinal Cord Injury-induced Immune Depression Syndrome (SCI-IDS) [4-9]. Presence of SCI-IDS has been verified independently after experimental [10] and human SCI [11]. In brief, SCI 'neurogenically’ ablates the immune system and enhances susceptibility to develop infections, which in turn might cause a generalized wound healing impairment – also affecting wound-healing/repair of the spinal cord lesion itself. Of note, besides increasing the mortality, infections represent an independent risk factor for impaired functional neurological recovery e.g. by i) reducing the conversion rate from being 'completely’ to 'incompletely’ paralyzed and ii) impairing gain of American Spinal Injury Association (ASIA) motor scores [12].

Based on preclinical and first clinical observations within a pilot trial [5,6] we aim to develop prognostic surrogate parameters in order to predict and selectively identify patients 'at risk’ to develop infections. Here, we propose to establish parameters after human SCI, which have been tested in other clinical paradigms of elevated infectious risk such as status post cardiopulmonary bypass [13] and after ischemic CNS injury [14,15]. Therefore, we apply methods established in humans, such as human leukocyte antigen (HLA)-DR expression on monocytes [14] and Concanavalin A (ConA)-induced cytokine expression in whole blood samples, as surrogate markers of SCI-IDS. HLA-DR expression on monocytes serves as primary outcome measure. Moreover, a peripheral blood leukocyte mRNA expression profile encoding for immune modulatory proteins will be investigated to sense and therefore predict an evolving immune suppression as early as possible. Furthermore, we will measure the presence of individual predisposition for infections by assessing polymorphisms in coding areas of MHC-proteins, toll-like pattern-recognition receptors and selected cytokines [16].

The prevention of infections facilitated by the 'neurogenic’ immune suppression syndrome (with its pronounced penetrance referred to as 'immune paralysis’) aims to (i) decrease mortality, (ii) reduce expensive hospitalization time and, (iii) improve the functional outcome, since SCI patients suffering infections are prone to develop inferior neurological recovery [12]. Molecular treatment strategies aiming to foster axonal plasticity and repair might be complemented by approaches that intend to protect the intrinsic neurological recovery potential. Given a realistic therapeutic timeframe of opportunity after SCI, the early identification of SCI-patients 'at risk’ would offer a 'preventive’ option to treat infections earlier and thereby avoid their detrimental consequences. This protective strategy might save neurological function 'at risk’ and thereby improve quality of life. In addition, it would be possible to unmask putative confounding factors that influence neurological outcome measures of relevance for interventional or rehabilitative trials [12].

A solid body of evidence demonstrates that SCI is associated with an early onset of immune suppression (SCI-IDS). Identification of SCI patients as immune compromised is a clinically relevant finding, yet widely underappreciated and warranting further analysis. In order to decipher the underlying mechanisms of SCI-IDS we are following-up on experimental results [5,7,10,17], clinical pilot trials [6,8], and cohort studies [9,18,19] with the international SCIentinel trial. We outline the study protocol and design, define the main outcome parameters, and provide the results of an administrative interim analysis.

## Methods/Design

### Study design, study coordination, and participating centers

The “SCIentinel” trial is designed as a prospective multicenter study for the detailed evaluation of the SCI-IDS (Figure 1). The overall coordination is performed by the Department of Experimental Neurology, Clinical and Experimental Spinal Cord Injury Research (Neuroparaplegiology) at the Charité University Hospital, Campus Mitte, Berlin, Germany.

### Duration

A recruitment period of 30 months is scheduled. Each patient will be followed-up to three months post-trauma. After completion of recruitment and follow-up, a further six months period is planned for the database clearing, the statistical evaluation and the preparation of the trial report. Enrolment has started in August 2011. Expected study completion date is the first quartile of 2014. Publication of the trial report is scheduled for the end of the year 2014.

### Ethics

The protocol received approval by the local Ethics Committees: Ethical Committee of the Charite – Universitätsmedizin Berlin (EA1/001/09), University Health Network Research Ethics Board, Toronto (REB10-0384-AE), Cantonal Ethics Commission, Zurich (KEK-ZH-Nr. 2011–0059). Participants will be informed about the trial, orally and in written form, using patient’s information sheets and written informed consent will be obtained. This study complies with the Helsinki Declaration, the principles of Good Clinical Practice (GCP) and the Personal Data Protection Act. The study will also be carried out in keeping with local legal and regulatory requirements. The study has been registered in the German Clinical Trials Registry (DRKS-ID: DRKS00000122).

### Participants

A number of 118 patients is planned to be allocated to the study for examination of the primary endpoint. In order to allow for investigation of the role of disturbed innervation of the major splanchnic nerve (T5-T9) as linked to alterations of the immune system function, we categorize SCI patients into lesions with the neurological level T4 or above versus lesions neurological level T5 or below. Therefore, the patients will be assigned to 3 groups: i) 48 SCI-patients with a neurological level T4 or above; ii) 31 patients with a neurological level T5 or below; iii) 39 patients with an acute vertebral fracture, but without SCI as control group (Figure 2).

**Figure 2 F2:**
[figure not shown]
**Relay-interaction of the immune system and the central nervous system.** Legend: Groups for primary comparison in relation to the major sympathetic outflow (vegetative innervation). In Group I (SCI of the neurological level T4 or above) the lesion is localized within the spinal segments C2-T5, resulting in a disturbance of the sympathetic innervation of immunologically relevant organs through the coeliac ganglion and further ganglia connected through lower segments of the spinal cord. Of note, the neurological level is defined by the ISNCSCI as the most cranial segment with normal sensory function and a muscle grade of at least 3/5 with normal function in the segments above on both sides of the body, i.e. in case of a neurological level T4, the lesion begins in the segment T5. In Group II (SCI of the neurological level T5 or below) the lesion is located in the spinal segment T6 or below. Thus, the sympathetic outflow to the coeliac ganglion is expected being only partially disrupted or completely preserved. Group III consists of patients with vertebral fracture alone without injury to the spinal cord (control). Here, the sympathetic innervation is intact.

The study will not interfere with methylprednisolone treatment per site regimens and patients will be also enrolled, but are excluded from the analysis of the primary endpoint. Based on experiences from the clinical practice in the recruiting trial centers the rate of cases treated with methylprednisolone is estimated to be 5-10%. Thus, up to 12 patients will additionally be included for explorative examination of methylprednisolone-related alterations of the immune system after SCI (Figure 2).

### Sample size calculation

The primary endpoint is a difference in HLA-DR expression on monocytes exactly quantified by analysing antibody-binding molecules/cell within the first week (day 3–4) post-trauma. Numbers of patients to be enrolled were calculated on the basis of a pilot study (n = 26) [6]. The sample size calculation was performed for an effect size of 0.18. The type one error was be set to 0.05 (two-sided); type two error was set to 0.2. The number of patients eligible for evaluation (for testing the hypothesis by the one way anova) is 56 in total (software nquery, version 7.0). Due to an expected rate of drop-outs/missing data of 50% and non-parametric testing, where applicable, the number of patients to be recruited increases to 118 in total. The expected rate of drop-outs/missing data relates to the structural conditions of acute SCI care in terms of i) delayed transfer to specialized SCI trial centers after primary care in external non-specialized centers and ii) loss to follow up due to discharge from inpatient rehabilitation, particularly in the control group or in cases of mild incomplete SCI. Consequently, to allow for a completion of the study within a feasible time period consideration of missing values is unavoidable.

The sample size calculation was performed taking the asymmetric natural distribution of the neurological lesion level into account [20]. Injury to the cervical and high thoracic spinal cord has the highest incidence and represents the largest group of SCI patients. Thus, the relation of the 3 groups to each other was determined as follows based on the pilot trial data i) 41% (n = 48); ii) 26% (n = 31); iii) 33% (n = 39).

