**Figure 3 F3:**
[figure not shown]
**Longitudinal trial design.** Legend: Assessment points and time frames. The starting point of the time line is the time of injury not the time of surgery. In the case of difficulties in scheduling the visits 2 to 5 may be conducted within the indicated time windows (*italic*). The circadian rhythmics are respected.

At the 5 study visits, equal blood samples and clinical data will be obtained. The clinical data comprise infections, medication, surgery, and blood transfusions. The first assessment should be completed as early as feasible after the injury, preferably before surgery, otherwise at least within 31 hours post-injury. The second assessment point refers to a time window of 31–55 hours post-injury. To ensure a sufficient time interval to the first assessment the second one should be performed on the following day at the earliest. This allows a better intra-individual analysis. The visits 3, 4 and 5 refer to day 7, 14 and to 10 weeks after injury, respectively. Blood withdrawals, except at time point 1 should be performed between 7:00 and 11:00 am. This setting determines the influence of the circadian rhythm to a minimum.

In the case, if it is unavoidable that a patient may be assigned to the study later as 31 hours (delayed recruitment) e.g., due to later admission or transfer to a study center (see also sample size calculation), study inclusion is tolerated at any later time point. In individual cases of delayed recruitment or patient’s absence, documentation of visits 2–5 may be scheduled in extended time windows (Figure 3).

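### The primary endpoint is timed at day 3–4, which does not match the visit schedule, and the analysis section names no single visit as primary

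*Protocol article*

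**What the plan says.** All references are to the protocol article.

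- **Endpoint.** Sample size calculation gives the primary endpoint as a difference in monocytic HLA-DR, "exactly quantified by analysing antibody-binding molecules/cell within the first week (day 3–4) post-trauma".
- **Schedule.** The Methods/Design part of the abstract states: "The assessment points are: i) <31 hours, ii) 31–55 hours, iii) 7 days, iv) 14 days, and v) 10 weeks post-trauma". The Assessment time points section repeats this: "The second assessment point refers to a time window of 31–55 hours post-injury", and "The visits 3, 4 and 5 refer to day 7, 14 and to 10 weeks after injury, respectively".
- **Time origin and clock time.** The legend of Figure 3 says: "The starting point of the time line is the time of injury not the time of surgery". The text adds: "Blood withdrawals, except at time point 1 should be performed between 7:00 and 11:00 am".
- **Exceptions.** Assessment time points tolerates inclusion after 31 h. It allows visits 2 to 5 in extended windows for individual cases of delayed recruitment or absence. The limits of those windows are in Figure 3, which is not shown.
- **Analysis.** Statistical analysis describes the primary-endpoint analysis as a three-group comparison at the early and the later visits, by one-way ANOVA or a non-parametric test. It singles out no visit.

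**The concern.** A primary endpoint should lead to one sample per patient and one test. Here the endpoint carries a time label that appears nowhere in the visit schedule, and the analysis section does not supply the link. A reader of the article cannot tell with certainty which draw gives the primary result.

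What is at stake is the status of the main test. If several visits can each be presented as the primary comparison, the 5% error rate in the sample size calculation is not attached to a defined test. The set of patients contributing to the primary result also depends on a choice that has not been written down.

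**Working it through.** **1. The plan's own sample size.** Inputs from Sample size calculation: effect size 0.18, two-sided alpha 0.05, type two error 0.2, three groups, one-way ANOVA, 56 evaluable, 118 recruited. The article does not say what kind of effect size 0.18 is. Read as the variance ratio f², the noncentrality is λ = N × 0.18.

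- N = 56: power 79.5%.
- N = 57: power 80.3%, the smallest N reaching 80%.

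So 56 is reproduced to within one patient. With 50% loss, 56 / 0.5 = 112. The step to 118 is attributed to non-parametric testing without a figure; an assumed 5% gives 112 × 1.05 = 117.6, or 118. No input refers to a visit, so the stated number stays the same whichever visit is named.

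**2. Day 3–4 in elapsed hours against the scheduled windows.** Overlap = max(0, min of the upper limits − max of the lower limits).

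| Reading of day 3–4 | Visit 1 (<31 h) | Visit 2 (31–55 h) | Visit 3 (day 7, 168 h) |
|---|---|---|---|
| 72–96 h | 0 | 0 | 0 |
| 72–120 h (day 4 counted whole) | 0 | 0 | 0 |
| 48–96 h (third and fourth 24-hour periods) | 0 | 55 − 48 = 7 h | 0 |

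At most 7 of the 24 hours of visit 2 (7/24 = 29%) lie in day 3–4.

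**3. Day 3–4 in calendar days, injury day = day 1.** Let the injury occur at clock hour t (0 ≤ t < 24) and the draw at hour h (7 ≤ h ≤ 11) on day d. Elapsed time is 24(d − 1) + h − t, and visit 2 requires 31 to 55 h.

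- Day 2: 24 + h − t ≥ 31 needs h ≥ 7 + t, which is possible only for t ≤ 4.
- Day 3: 48 + h − t ≤ 55 needs h ≤ 7 + t. For t ≥ 4 the whole 7:00–11:00 slot qualifies; for t < 4 only its early part does.
- Day 4: 72 + h − t ≤ 55 needs h ≤ t − 17, which is below 7 for every t < 24, so it is never possible.

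Under this convention a regular visit 2 draw is on day 3 for any injury from 04:00 onward, on day 2 or 3 for earlier injuries, and never on day 4.

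**4. Completeness at the interim.** Table 5 uses the 56 patients feasible for per-protocol analysis (60 enrolled less 4 drop-outs).

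- Visit 2: 20 + 6 + 12 = 38; 38/56 = 68%.
- Visit 3: 22 + 8 + 14 = 44; 44/56 = 79%.
- Smallest group (T5 and below): 6/11 = 55% at visit 2 and 8/11 = 73% at visit 3.

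The legend to Table 5 calls 60% completeness acceptable, but nowhere reports completeness for the primary time point as such.

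**The case against.** The best defence is that visit 2 is in effect day 3. Its limits fit a morning draw on the third calendar day (31 = 24 + 7 and 55 = 48 + 7), and step 3 shows that this works for every injury from 04:00 onward. This stands as a plausible account of what was intended. It does not close the gap: the article states no such convention, it measures time from the injury itself, day 4 stays outside the regular window, and visit 2 is still not named as primary.

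A second defence is that the extended windows may reach day 4. That cannot be excluded without Figure 3, and late entry is foreseen in the design. But the text keeps those windows for individual cases, so they do not define the regular primary sample.

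A third is that an article condenses the protocol, and the full document may link the endpoint to a visit. It may. The point here is not an omission, however: the endpoint time and the visit schedule are both printed, and they do not agree as written.

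Several stronger readings are tempting and are not supported:

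- That no scheduled sample can fall on day 3–4, or that only stray samples would be left. Visit 2 falls on day 3 under one reasonable convention.
- That visit 3 is an equal candidate for the day 3–4 label. Day 7 does not match it under any counting; visit 3 comes in only through the open wording of the analysis section.
- That HLA-DR changes enough over these days to alter the answer. The article gives no time course after spinal cord injury.
- That the power statement belongs to no visit. The effect size comes from a pilot study that is not at hand, so this cannot be checked.

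**Conclusion.** The concern holds as a mismatch of definition. Counted from injury, the regular visit 2 window shares 0 to 7 h with day 3–4 and visit 3 shares none. Counted in calendar days from an injury day of 1, visit 2 supplies day 3 but not day 4. Because the analysis section spreads the primary endpoint over early and later visits, more than one comparison could be called primary. Completeness differs by 6 of 56 patients (68% against 79%) between visits 2 and 3.

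This rests on the windows printed in the text; the extended windows are unseen. It says nothing about the direction or size of any effect on the result, and it is no criticism of the sample size arithmetic.

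**What to change.** Reconcile Sample size calculation, Assessment time points and Statistical analysis before HLA-DR is compared between groups:

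- Name one visit and its hour window as the primary time point. Visit 2 (31–55 h post-injury) is the natural choice, as the only scheduled visit that can match day 3–4. If the day label is kept, state how days are counted.
- State whether and how a visit 2 sample taken in an extended window counts towards the primary analysis.
- Make the comparisons at all other visits secondary.
- Report completeness for the named visit and window.

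The cost is a few sentences and a dated amendment note. No extra samples or patients are needed and the recruitment target of 118 is unaffected. The interim evaluation in the article covers only recruitment and completeness, so as far as the article shows, the choice can still be made without knowledge of group differences.

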### Enrolment and eligibility criteria

With the seven study centers treating 20 to 60 acute SCI patients admitted to the emergency ward of each center per year we estimate to screen about 200 SCI patients per year and about 40 of them are expected to meet eligibility criteria (Table 1).

**Table 1 T1:** Eligibility criteria

**Inclusion criteria**	
(1)	Patients with acute isolated spinal cord injury (AIS A-D) planned for surgical stabilization and decompression, lesion may include more than 1 segment
(2)	Patients with acute isolated spinal fracture planned for surgical stabilization, lesion may include more than 1 segment
(3)	≥ 2 spinal cord or vertebral lesions definable one from another
(4)	Legal age of the patient
(5)	Documented informed consent of the patient
**Exclusion criteria**	
(1)	Non-traumatic spinal cord injury
(2)	2 or more spinal cord or vertebral lesions definable one from another
(3)	Severe polytrauma *(definition: patients with severe injuries of life-sustaining organ systems, which per se and in the acute phase are life-threatening (e.g., severe pelvic trauma, severe body cavity injuries)*
(4)	Concomitant traumatic brain injury (TBI) *(definition: i) Patients with persisting neurological deficit in consequence of the TBI, ii) patient with severe TBI (Glasgow Coma Scale ≤ 8), and iii) patients with intracranial pressure monitoring sensors.)*
(5)	Neoplasia and/or antineoplastic therapy
(6)	Rheumatic disease, collagenosis, vasculitis or other autoimmune disease
(7)	Preexisting chronic infectious disease (before the injury)
(8)	Preexisting systemic steroid treatment
(9)	Severe alcohol or drug addiction
(10)	Pregnancy, lactation

Investigators will evaluate the patients after admission to the emergency ward for eligibility. Before final inclusion into the study the investigator will conduct an interview with the patients to verify the inclusion- and exclusion-criteria and obtain written informed consent.

